### Outcomes

The primary outcomes for this trial are the changes in the visual analogue scale (VAS) for diarrhoea, abdominal pain, mucus in the stool, and bloody purulent stool. The secondary outcomes will include the TCM syndrome scale, the Short Inflammatory Bowel Disease Questionnaire (SIBDQ), the Rating Form of Inflammatory Bowel Disease Patient Concerns (RFIPC), and the Short Health Scale (SHS). Efficacy indicators for each subject will be observed and recorded before the study and at the end of each period (including week 8, week 16, week 24, week 32, week 40, and week 48).

Patients will be asked to rate their diarrhoea, abdominal pain, mucus in the stool, and bloody purulent stool severity by placing a vertical mark on a 10-mm horizontal VAS. The left and right extremes of the VAS are labelled ‘the lightest’ and ‘the most serious’, respectively.

The (TCM) Traditional Chinese medicine syndrome scale is an efficacy evaluation of six items measuring dampness, stagnancy due to spleen deficiency syndrome: diarrhoea, bloody purulent stool, anorexia, abdominal distension, limb burnout, and disinclination to talk due to mental weariness. Each item is rated from 0 to 3. The higher the scale, the more serious is the dampness stagnancy [11].

The SIBDQ uses 10 items derived from the inflammatory bowel disease questionnaire, which explain 90% of the variance in the SIBDQ for UC patients. The total score ranges from 10 (worst health) to 70 (best health). This gauge of subjective health status or quality of life in patients can be administered and scored quickly and easily [31].

The RFIPC is a self-administered form containing 25 items of concern related to inflammatory bowel disease. Each item is rated from 0 to 100 on a VAS form. The average score of all 25 items is the ‘sum score’. A higher score indicates a higher level of patient anxiety [32].

The SHS is a disease-specific questionnaire consisting of four items measuring four dimensions of health: bowel symptom severity, social functioning in daily life, disease-related worry, and perceptions of general well-being. Item responses are indicated on a 100-mm VAS from 0 to 100. The higher the scale, the more serious are the health concerns [33].

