### Participants

All UC patients will be enrolled from the First Affiliated Hospital of Guangzhou University of Chinese Medicine (GZUCM). Ethical approval was obtained from the Ethics Committee of The First Affiliated Hospital of GZUCM.

The patients will be included if they meet the following inclusion criteria:
Patients diagnosed with UC in the remission phase (determined by a UC Disease Activity Index score of 0–2 and a bloody stool score of 0) according to ‘The Asia-Pacific consensus on ulcerative colitis’ promulgated by APAGE on Inflammatory Bowel Disease in 2010 [6]Patients diagnosed with dampness, stagnancy, and spleen deficiency syndrome according to ‘The experts of TCM consensus on ulcerative colitis (2017)’ promulgated by the Spleen and Stomach Diseases Branch of the Chinese Society of TCM [11]. The symptoms included abdominal distension and pain, relatively high frequency of stool, production of thin faecal matter, a red and white, sticky, jelly-like stool or indigested food in the stool, pale complexion, mental fatigue, pale tongue with greasy coating (moss), and weak pulsePatients aged between 18 and 75 yearsPatients who agree to voluntary participation in this study, sign the informed consent form, and have good compliance

The patients will be excluded according to the following criteria:
Patients with active UC, severe UC, or the acute fulminating type of UCPatients undergoing treatment with corticosteroids (orally administered, enemas, suppository, or injectable solution)Patients treated with blood-cell apheresisPatients who were administered anti-tumour necrosis factor-a antibody within 90 days before starting the study drugPatients with a history of hypersensitivity to mesalazine and salicylic acidPatients with serious cardiovascular disease, haemodyscrasia, or lung disease or with a history of these conditionsPatients with liver disease or kidney diseasePatients with a malignant tumour as a complication;Pregnant women or those who are breastfeeding

Patients will be withdrawn from the trials if they meet the following criteria:

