### Interventions

Patients in the intervention period will be treated with 300 ml modified SJZD granules and 1 g mesalazine placebo three times each day, while patients in the control period will be given 1 g mesalazine three times and 300 ml modified SJZD granules placebo each day. Each period lasts for 8 weeks.

Modified SJZD is a combination of *Radix pseudostellariae* (*Taizishen*), *Atractylodes macrocephala* (*Baizhu*), Poria (*Fuling*), *Portulaca oleracea* L (*Machijian*), *Rhizoma cimicifugae* (*Shengma*), *Citrus aurantium* L (*Zhike*), and *Agastache rugosa* (*Huoxiang*). If the symptom of bloody purulent stool is severe, *Polygonum chinense* L (*Huotanmu*) and *Crinis carbonisatus* (*Xueyutan)* will be added. If the symptoms of tenesmus are severe, *Verbena officinalis* L (*Mabiancao*), *Paris yunnanensis* Franch (*Chonglou*), and *Indigo naturalis* (*Qingdai*) will be added. All ingredients will be manufactured as a Chinese herbal granule by Guangdong Yifang Pharmaceutical Co. Ltd. Mesalazine enteric-coated tablets ([name] GmbH, Freiburg, Germany) will be used in the study. Guangdong Yifang Pharmaceutical Co. Ltd. makes both of the placebos, which have an identical shape, colour, and weight as the active drugs.

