### Sample size

Based on published data [20], whose primary outcome was the VAS score of mucus in the stool, the standard deviation of self-efficacy was 0.8, and the difference value of efficacy between the two groups was 0.7. We assume that there is no difference in efficacy between each patient. Assuming a two-sided significance level of 0.05 and power of 80% (*α* = 0.05, *β* = 0.2), the sample size is calculated as 8 (fixed model) [29]. Considering a 20% loss to follow-up, the sample size was 10 cases.

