### Statistical methods

All data will be recorded and collected on the CRFs by the researchers. The data will be input using EpiData 3.0 (EpiData Association, Odense, Denmark). To ensure the accuracy and integrity of the data, double data entry and proofreading will be performed by two independent researchers.

R software (version 3.6.2) will be utilised for the statistical analysis. A *P* value ≤ 0.05 will be considered statistically significant. For the quantitative indicators, the mean and standard deviation or the median and interquartile range will be calculated. Descriptive statistics will be used to summarise the demographic characteristics of the participants, including age, sex, and extent of UC.

For the individual *N*-of-1 trials, paired *t* tests or Wilcoxon signed-rank tests will be used to compare the efficacy (including the VAS for diarrhoea, abdominal pain, mucus in the stool, and bloody purulent stool, as well as all the QOL scores) of modified SJZD with that of mesalazine. For individual patient reports, the VAS for diarrhoea, abdominal pain, mucus in the stool, and bloody purulent stool, as well as all the QOL scores and safety indicators reported, will be described, as will whether the efficacy is within the range of significant improvement.

To synthesise the data from the *N*-of-1 trials from all patients (including the VAS for diarrhoea, abdominal pain, mucus in the stool, and bloody purulent stool, as well as all the QOL scores), a paired *t* test was used for the analysis. Considering the correlated data structure, we also used a mixed model. The equation for the mixed model is as follows [34]:

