## Discussion

A sufficient washout period is necessary for *N*-of-1 trials because the latter intervention may be affected by the carryover effects of the previous intervention. However, the patient does not receive effective treatment during washout periods. Therefore, including a washout period would be inappropriate for UC patients. For patients with UC in the remission phase, insufficient treatment leads to acute UC or aggravation of UC [36, 37]. Therefore, there are no washout periods in our study.

Although there are no washout periods in this study, we considered that the carryover effects of modified SJZD have little effect in practice. The reasons are as follows: (1) the main active ingredients of SJZD are glycyrrhizic acid, glycyrrhetinic acid, pachymic acid, atractylodes lactone III, ginsenoside Re, and ginsenoside Rb_1_, and a pharmacokinetic study showed that their mean half-life is no more than 12 h [38]. For the other active ingredients of modified SJZD, further studies reported that their half-life is no more than 24 h [39–45] and (2) even if there are carryover effects for modified SJZD, a mixed-effect model will be used to analyse the data from the *N*-of-1 trials. The mixed-effects model can estimate treatment effects accurately while controlling for carryover effects; it separates carryover effects from treatment effects in a series of *N*-of-1 trials [34].

The Mayo score is a general indicator used to assess the severity of active UC [6]. If the procedure for calculating the Mayo score is followed properly, the patients with UC would undergo enteroscopy after each period (one per month in the trial). This would be too frequent for patients to accept. Therefore, the Mayo score will not be used as the primary outcome. Diarrhoea, abdominal pain, and mucus in the stool are the most common symptoms for patients with UC. Bloody purulent stool was reported to have a close relationship with clinical relapse [46, 47]. For these reasons, the VAS scores for the main clinical symptoms (diarrhoea, abdominal pain, mucus in the stool, and bloody purulent stool) were chosen as the primary outcomes.

Our findings will be interpreted with caution. We anticipate that the results will show that modified SJZD is effective for patients with UC in remission.

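### Four symptom scales are each primary at an unadjusted 0.05 with no stated success rule, while the sample size covers only the mucus scale; the bloody-stool scale also starts at or near its floor

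*Protocol article*

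**What the plan says.** - **Outcomes.** "The primary outcomes for this trial are the changes in the visual analogue scale (VAS) for diarrhoea, abdominal pain, mucus in the stool", with bloody purulent stool as the fourth. The Discussion confirms that the four VAS scores "were chosen as the primary outcomes". No order, composite or all-must-succeed rule is given.
- **Statistical methods.** There is one threshold for everything: a P "value ≤ 0.05 will be considered statistically significant". Each scale is pooled across patients by a paired t test and also by a mixed model. No adjustment is described.
- **Sample size.** The standard deviation of 0.8 and the difference of 0.7 come from a published study "whose primary outcome was the VAS score of mucus in the stool". The calculation uses two-sided 0.05 and 80% power and gives 8 patients, or 10 after 20% loss. No figures are given for the other three scales.
- **Participants.** Remission at entry means "a UC Disease Activity Index score of 0–2 and a bloody stool score of 0". The syndrome criterion in the same list includes red and white jelly-like stool among its symptoms.
- **Interventions.** Extra ingredients are added "If the symptom of bloody purulent stool is severe".

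**The concern.** There are two linked problems.

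First, with four primary outcomes, one unadjusted threshold and no success rule, a result at or below 0.05 on any single scale could be reported as a positive primary result. The sample size spends the whole 0.05 on mucus. The design therefore leaves no room for a later adjustment without losing power, and no basis for judging power on diarrhoea, abdominal pain or bloody stool.

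Second, patients enter with a bloody stool score of 0 on the disease activity index. A primary outcome defined as change in the bloody-stool VAS then starts at or near the bottom of its scale. With 8 to 10 patients and mostly very low values, a paired t test on that scale is likely to carry little information, yet it has the same status as the other three.

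**Working it through.** **Inputs from the protocol.** Four primary scales; two-sided alpha 0.05; power 80%; SD 0.8; difference 0.7; 3 cycles per patient; the same treatment effect in every patient (Sample size, Trial design, Outcomes).

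**Reproducing the plan's figure.** Take 0.8 as the SD of one period's score, so a within-cycle difference has variance 2 × 0.8² = 1.28.

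- Normal approximation: n = 2·SD²·(z₀.₉₇₅ + z₀.₈₀)² / (k·δ²) = 1.28 × 2.8016² / (3 × 0.49) = 6.83, so 7.
- Noncentral t with 3n − 1 degrees of freedom: power is 77.0% at n = 7 and 82.7% at n = 8, so 8.
- Loss of 20%: 8 / 0.8 = 10.

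The stated 8 and 10 are reproduced, for one outcome at an unadjusted 0.05.

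**False-positive rate if success on any one scale counts.**

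| Situation | Rate |
|---|---|
| Four independent scales: 1 − 0.95⁴ | 18.5% |
| Upper bound under any dependence: 4 × 0.05 | 20% |
| Four scales, assumed common correlation 0.5 (simulated normal tests) | about 15.6% |
| Four scales, assumed common correlation 0.7 (simulated) | about 13% |
| Three independent live scales: 1 − 0.95³ | 14.3% |

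The protocol gives no correlations; 0.5 and 0.7 are assumptions that show the range. The last row applies if the bloody-stool scale is almost constant, because such a scale adds almost no false positives. The table counts one test per scale and does not price the second pooled analysis.

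**Cost of adjusting at the planned size.** Bonferroni level: 0.05 / 4 = 0.0125. Power for the mucus scale on the protocol's own inputs, with two choices of degrees of freedom (2n if patients are fitted as blocks, 3n − 1 if all differences are pooled):

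| Patients | Level | Power, 2n df | Power, 3n − 1 df |
|---|---|---|---|
| 8 | 0.05 | 81% | 83% |
| 8 | 0.0125 | 59% | 63% |
| 10 | 0.0125 | 73% | 76% |

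On the pooled version, 11 patients are needed at 0.0125 (power 81.1%), and 11 / 0.8 = 13.75, so 14 after loss.

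**Bloody stool, statements side by side.** The entry rule sets the index item to 0. The syndrome criterion in the same list includes red and white jelly-like stool. The Interventions section provides for severe bloody purulent stool. The first two apply to the same patient at the same time and sit uneasily together. The third is conditional and may refer to symptoms that appear later.

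**The case against.** **Multiplicity rules often sit in the statistical analysis plan, which is not shown.** This is fair as far as it goes. But the protocol itself fixes four primary outcomes and sizes one of them at the full 0.05. An adjustment added later would not restore the power that it costs, and an all-must-succeed rule would need sizing for the other three scales.

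**The inflated rate presumes that any one success counts.** This stands as a condition. If all four had to succeed, the overall error rate would not exceed 5%. The protocol does not say which rule applies, and that silence is part of the problem.

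**A reader might take 18.5% as a ceiling.** It is the independence value. The ceiling is 20%, and positive correlation or a nearly constant scale lowers the rate. Four live tests and one inert test cannot both be assumed.

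**A reader might conclude that the bloody-stool outcome cannot improve, or that a null result on it says nothing.** The documents do not support this. The zero is on the disease activity index, not on the patient-rated VAS. The analysis compares treatment periods, so a difference can arise if bleeding returns more under one treatment. The Discussion chose the outcome for its link to clinical relapse. What stands is little room to fall from entry and little expected variation.

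**A reader might also infer that anyone who worsens is withdrawn.** The withdrawal criterion requires worse symptoms together with a rise of at least 30% in the Mayo score, so a rise on the bloody-stool VAS alone does not trigger it.

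**A reader might see the Interventions text as contradicting the entry rule.** It is a contingency over 48 weeks of treatment in a relapsing disease, so it is not a strict contradiction. The sharper tension is between the two entry criteria.

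**The Discussion gives clinical reasons for all four symptoms.** They are reasons to measure all four, and they do not supply a success rule.

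**Conclusion.** The point holds in this form. Four scales are primary at an unadjusted 0.05, no success rule is stated, and only the mucus scale is sized. If any one success counts, the false-positive rate is about 18.5% under independence and at most 20%. It is about 15.6% or 13% at assumed correlations of 0.5 or 0.7, and about 14.3% with three independent live scales. Each is more than twice the nominal 5%. The power figures assume that the protocol's SD is that of a single period's score and that the treatment effect is the same in every patient.

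The bloody-stool scale is a poor primary outcome because it starts at or near its floor and is expected to vary little. It can still show a treatment difference through the return of bleeding.

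**What to change.** 1. Name the mucus VAS, which sized the trial, as the single primary outcome at two-sided 0.05.
2. Make the VAS for diarrhoea and for abdominal pain secondary, with Holm adjustment across the two.
3. Report bloody stool as any occurrence per period, by treatment.
4. Reconcile the statements on bloody stool: the two entry criteria in Participants with each other, and both with the conditional addition in Interventions.

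**Cost.** Amended wording in the protocol and the registration. The sample size of 10 and the planned power are kept. The downside is that three symptoms lose primary status, although the Discussion argues for each.

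**If the sponsor keeps all four as primary:** state the success rule. If any one success counts, apply Holm across the four and restate the power. Holm's first step uses 0.0125, where power for the mucus scale is 59–63% with 8 patients and 73–76% with 10. If all four must succeed, no adjustment is needed, but the other three scales need their own design assumptions.

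### The four primary VAS outcomes are specified on a 10-mm line with no score range or unit, so the planned difference of 0.7, if in millimetres, is smaller than a 1-mm reading of any single mark

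*Protocol article*

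**What the plan says.** The primary outcomes are changes in the VAS for diarrhoea, abdominal pain, mucus in the stool and bloody purulent stool. Protocol article, Outcomes, says that patients rate each symptom "by placing a vertical mark on a 10-mm horizontal VAS". The two ends "are labelled ‘the lightest’ and ‘the most serious’, respectively". No numeric range, unit or reading precision follows. In the same section the Short Health Scale, a secondary outcome, has both its length and its range: "Item responses are indicated on a 100-mm VAS from 0 to 100".

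Protocol article, Sample size, takes its inputs from a published study "whose primary outcome was the VAS score of mucus in the stool". It states that "the standard deviation of self-efficacy was 0.8" and that "the difference value of efficacy between the two groups was 0.7". Neither figure has a unit. From these, with two-sided 5% significance, 80% power and a fixed model, it derives 8 patients, raised to 10 for 20% loss to follow-up.

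Nothing elsewhere in the article changes the line length or says how the VAS is scored.

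**The concern.** The line length is a stated value for the instrument behind every primary outcome. It is not a detail left to another document, and a form designer who follows the article will print a 1-cm line. Read in millimetres, that line makes the planned treatment difference 0.7 mm and the planned standard deviation 0.8 mm. Both lie below one division of an ordinary ruler.

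Two things are at stake. The first is measurement error: reading and marking errors that hardly matter on a 100-mm line become a material share of the variance on a 10-mm line. This weighs most on the individual-patient analyses in Statistical methods, where each patient contributes only three pairs. The second is interpretation: without a unit, a reader cannot tell what size of symptom change 0.7 stands for, or whether 0.7 and 0.8 belong to the scale that will be used.

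**Working it through.** **Inputs from the article.** Difference δ = 0.7; standard deviation s = 0.8; two-sided α = 0.05; power 80%; fixed model; 20% loss to follow-up (Sample size). Cycles per patient k = 3 (Trial design). Line length 10 mm (Outcomes).

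**1. The plan's own figure.** Take 0.8 as the standard deviation of one period's score. The normal approximation for the number of A/B pairs is

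2s²(z₀.₉₇₅ + z₀.₈₀)²/δ² = 2 × 0.64 × (1.960 + 0.842)²/0.49 = 20.5 pairs.

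Divided by 3 cycles this is 6.83, or 7 patients. With the noncentral t distribution, the noncentrality at n patients is δ/√(2s²/(nk)):

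- n = 7: power 0.75 with n(k − 1) = 14 degrees of freedom, or 0.77 with nk − 1 = 20.
- n = 8: noncentrality 0.7/√(2 × 0.64/24) = 3.03; power 0.81 with 16 degrees of freedom, or 0.83 with 23.

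The smallest n that reaches 80% is 8, and 8/0.8 = 10. The stated figures reproduce.

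**2. Effect of the unit on n.** The calculation uses only δ/s = 0.7/0.8 = 0.875. Multiplying both figures by 0.1, 1 or 10 leaves 20.5 pairs, 8 patients and 10 after dropout.

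**3. What 0.7 is on paper.** The article does not fix the unit, so three readings are possible:

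- 10-mm line scored in mm (as printed): 0.7 mm, or 7% of the line.
- 100-mm line scored 0–10 (assumption): 7 mm, or 7% of the line.
- 100-mm line scored in mm (assumption): 0.7 mm, or 0.7% of the line.

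**4. Measurement error on the 10-mm line scored in mm.** Reading to the nearest 1 mm adds an error with SD 1/√12 = 0.29 mm. Any further marking error e is an assumption; 0.25 and 0.5 mm are shown as a range. Total SD = √(0.8² + 1/12 + e²). Power is at n = 8, k = 3.

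| Error added | Total SD | Noncentrality | Power, 16 df | Power, 23 df |
|---|---|---|---|---|
| None | 0.80 | 3.03 | 0.81 | 0.83 |
| 1-mm rounding | 0.85 | 2.85 | 0.76 | 0.78 |
| Rounding + 0.25 mm | 0.89 | 2.74 | 0.73 | 0.75 |
| Rounding + 0.5 mm | 0.99 | 2.46 | 0.64 | 0.65 |

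A simulation of 8 patients with 3 pairs each, analysed by paired t test, agrees with the second row. Rounding to 1 mm left the mean difference at about 0.70 and lowered power from about 0.83 to about 0.78.

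**5. The same errors on a 100-mm line scored 0–10.** Rounding to 1 mm becomes 0.1/√12 = 0.029 units, and a 0.5-mm marking error becomes 0.05 units. Total SD = √(0.64 + 0.0008 + 0.0025) = 0.802, and power stays at about 0.81–0.83.

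**The case against.** The strongest reply has four parts.

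*It may be a slip.* The 10 mm could be an error for 10 cm, and the Short Health Scale is a different instrument, so its 100-mm line contradicts nothing. Both are fair, but the article does not show that it is a slip. A wrong length left in the specification can be carried onto the case report form.

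*The result is still readable.* A reader might infer that a 0.7-mm difference cannot be detected at all on such a line. That does not follow. The limit applies to an individual mark. The trial's pooled analysis rests on a mean over about 24 pairs, which rounding leaves unbiased in the simulation and only somewhat less precise.

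*The power loss depends on inputs outside the article.* This stands in part. Rounding alone costs about five percentage points; anything beyond that comes from an assumed marking error. The 0.8 is also taken from published VAS data and may already contain marking and reading error, in which case adding it again counts it twice. If the source used a different line, 0.8 is not 0.8 mm and these figures do not apply. The source is not available here.

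*The sample size is unaffected.* A reader might infer that the calculation fails once the scale is corrected. It does not: n depends on 0.7/0.8, and a common rescaling leaves it alone. What is missing is the unit that links the two figures to the instrument.

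Reading precision can reasonably be left to the full protocol. The line length cannot be set aside on that ground, because the article states it.

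**Conclusion.** The point holds as a fault in the definition of the primary measurement. As written, the line is 1 cm long and unscored, and a difference of 0.7, if it is in millimetres, lies below a 1-mm reading of any one mark. On that reading, power at 8 patients falls from 0.81–0.83 to 0.76–0.78 through 1-mm rounding alone, just under the planned 80%. With a further assumed 0.25 to 0.5 mm of marking error it falls to between about 0.75 and 0.64. These figures assume scoring in millimetres and an SD of 0.8 that is free of the added error. The documents establish neither, so the lower figures show sensitivity and are not a forecast.

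The 8 and 10 patients stand. It would also go too far to say that 0.7 and 0.8 must mean 7 mm and 8 mm on a longer line, since the unit of the source study is not given.

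The left anchor is a lesser point. Its label names the mildest severity, not absence, although patients enter with a bloody stool score of 0 (Participants) and bloody purulent stool is a primary VAS. A mark at the left end is still the scale's minimum, so this is a matter of clarity.

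**What to change.** In Outcomes, replace the 10-mm line with a 100-mm (10-cm) line read to 1 mm, and state the numeric range of the score. In Sample size, give 0.7 and 0.8 in that unit after checking which scale the source study used. If the source's scale differs from the trial's only by a constant factor, convert both figures together; 8 and 10 then remain. As an option, label the left end as absence of the symptom.

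The cost is one corrected form template and a few sentences, with no change to the number of patients, the visits or the analysis. It should be done before the forms are printed, because marks made on a 1-cm line cannot be recovered at finer resolution afterwards.
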